### 2.6. Description of Procedures

#### Measure of Frailty: EFT and SPPB

The EFT is a brief four-item (chair rise, cognitive status, hemoglobin, and serum albumin) frailty scale [8]. The EFT is scored 0 (least frail) to 5 (most frail). The prevalence of frailty was defined according to the EFT score, specifically EFT ≥ 3 out of 5.

The SPPB is an objective tool measuring the physical performance status with recognized prognostic values for multiple frailty-related outcomes [12,13,14]. The SPPB is calculated by the time spent or needed to complete multiple tasks: standing balance, usual gait speed, and five chair tests. The timed results of each subtest are rescaled according to predefined cutoff points for obtaining a score ranging from 0 (most physically frail) to 12 (least frail/best performance) [14,15].

### 2.7. Human Biological Sample Biomarker Collection and Analysis

The collection of samples for biomarker research is part of this study. Plasma was collected from all participants in this study at baseline and was collected at the end of follow-up.

To identify novel biomarkers able to identify frailty and predict its progression, we used plasma samples collected during the frailty evaluation to identify miRNAs and inflammatory proteins cross-sectionally associated with frailty. Such candidates are derived from an unbiased miRNOmic analysis and a focused proteomic analysis. Statistical analysis revealed which markers (and relative combinations) identify a frail status. Then, after dosing such candidate molecules in the whole cohort, we performed statistical analyses to explore if such markers are also able to predict the eventual improvement or deterioration in frailty at follow-up, after intervention.

### 2.8. Six-Minute Walk Test (6MWT)

The 6MWT was performed in an indoor 60 m long corridor, according to the recommendations of the American Thoracic Society [16]. All patients were instructed to walk along the corridor from one end to the other at their own pace, as many times as possible in the permitted time. After 6 min had elapsed, the patients were instructed to stop walking, and the total distance walked was determined. This test was supervised by a physical therapist who encouraged the patients in a standardized fashion at regular intervals.

### 2.9. Measure of Quality of Life: EuroQol (EQ) Visual Analog Scale (VAS)

The EQ VAS is a measure of self-reported health outcomes, based on a visual analog graduated scale (0 to 100) for assessing health status, ranging from the worst imaginable health state (0) to the best imaginable health state (100) [17].

### 2.10. Measure of Comorbidity: Cumulative Illness Rating Scale (CIRS)

Pre-existing comorbidities were assessed using the CIRS, which gives a severity score and comorbidity score. This index is based on the scoring (from 0 to 4) of disease severity for 14 items corresponding to organs that may be affected by chronic disease. The CIRS severity score can be calculated as the average of each CIRS item score. The CIRS comorbidity score is based on the count of organ systems with moderate-to-severe impairment [18].

### 2.11. Measure of Nutritional Status: Mini Nutritional Assessment (MNA)

The MNA is a screening tool aimed at assessing nutritional status in older patients through 18 questions in 4 areas (basic anthropometrics, dietary intake, global indicators and self-assessed health status). Individuals with a score of 24–30 are considered to have a normal nutritional status, a score of 17–23.5 suggests a risk of malnutrition, and a score of <17 identifies malnutrition [19].

### 2.12. Cognitive Status: Mini Mental State Examination (MMSE)

Global cognitive function was assessed by the MMSE. In clinical practice, MMSE is used to detect cognitive impairment, monitor cognitive decline over time, and evaluate the impact of potential treatments on cognition (particularly in older adults). It is brief, easily administered, and quickly scored. The measure assesses orientation, attention and calculation (Serial 7s, spell “world” backward), language (naming, repetition, comprehension, reading, writing, copying), and immediate and delayed recall. Scores > 24 indicate normal cognitive status, while lower scores indicate cognitive impairment [20].

### 2.13. Depression: Geriatric Depression Scale (GDS)

The GDS is a self-administered test developed for a brief screening of depression in older persons. The 15-item short form (GDS-15) was used for this study [21]. Scores may range from 0 (no depression) to 15 (severe depression). Answers are dichotomic to facilitate understanding and answering in older individuals. The questions can be read to patients. The GDS correlates highly with well-studied measures such as the Beck Depression Inventory, Zung Depression Inventory, and Hamilton Rating Scale for Depression [21].

### 2.14. Functional Independence: Barthel Index for Activities of Daily Living (ADLs)

The Barthel Index measures functional disability in 10 ADLs by quantifying patient performance. Five-point increments are used in scoring, with a maximal score of 100 indicating full independence whilst the lowest score of 0 indicates a patient with a completely bed-bound state [17].

### 2.15. Adherence to Therapy: Morisky Medication Adherence Scale (MMAS-8)

MMAS-8 is an 8-item, structured, self-measured, self-reported measure that assesses medication adherence [22].

### 2.16. Anthropometric Measures

The patients were weighed before breakfast without their shoes, and Body Mass Index (BMI) was calculated as [weight (kg)]/[height (m)]^2^.

### 2.17. Laboratory

Complete blood counts and creatinine, total cholesterol, hemoglobin, albumin, and NT-proBNP levels were measured as in routine clinical practice. The Glomerular Filtration Rate (eGFR) was estimated by the Cockcroft–Gault formula.

### 2.18. eHealth Home-Based CR Program

A multidisciplinary home-based CR program was implemented for Group A patients. The program lasted a maximum of 6 months; it was coordinated by a cardiologist and it was based on a multidisciplinary intervention by different healthcare providers: a nurse (case manager), physiotherapist, psychologist, and dietician.

The protocol was shared between the investigators involved in the two centers and was developed based on the most recent guidelines [5]. The online platform used for the intervention had a pre-specified list of questions and items to check, including the vital parameters to be collected at each visit, in order to maximize standardization and the fidelity of the programs between the two centers involved.

In the present study a synchronous model of cardiac TR, based on a real-time interaction between the patient and healthcare provider, was used. The advantages of this approach are that it allows a very close follow-up and better program personalization.

The core of the TR program was represented by scheduled video-calls with the patient (2 per week, 30–45 min duration each) by the nurse and physiotherapist focused on: education and cognitive training, exercise training session along with physiotherapy counseling once a week, assessment of healthy lifestyle, risk factor control, medication adherence and therapeutic targets. A video-call with a psychologist and dietician for psychosocial and nutritional counseling was provided at least once per fortnight. A social assistant was involved as needed by the nurse case manager.

The video-call was done by cell phone, tablet, or PC according to the patient’s preference.

For monitoring medication adherence and fall risk, one tool, i.e., text messaging, smartphone applications, or other electronic devices, tailored to the patient’s characteristics was applied. If applicable, an initial in-home visit to assess fall risk elements was also performed and a digital health alarm system to alert caregivers in case of physical discomfort was provided.

The program also included unscheduled calls from the patient in predefined time slots in case of need.

A pulse oximeter and a portable one-lead electrocardiograph for the telemonitoring of vital signs were available, and patients were able to call and be assisted in the case of urgent need or emergency, according to the internal standard operating procedure of each site.

Exercise training sessions were based on a ‘low level’ and a ‘high level’ of intensity, as detailed in the section below. The ‘low level’ consisted of 10–30 min of free exercise on a mini-ergometer (EverFit Welly M) without load and 30 min of callisthenic exercises, performed 3 times/week, and free walking twice a week. The ‘high level’ consisted of 30–45 min of free exercise on a mini-ergometer with incremental load, and 30–40 min of muscle reinforcement exercises using weights between 0.5 and 2.5 kg.

### 2.19. Exercise Training Protocol

All included individuals were subjected to the Short Physical Performance Battery (SPPB) to also evaluate balance and fall risk; based on the result obtained, they subsequently carried out a Six-Minute Walk Test (6MWT) to evaluate their functional capacity. The subjects were thus categorized into two groups based on the tests results: low level or high level (Figure 2). Subjects unable to perform a 6MWT for clinical and/or functional reasons performed only the SPPB.

The program included daily 30 min moderate-intensity aerobic training using a pedal exerciser and twice-weekly 30 min strength training using adjustable dumbbells and ankle weights according to the low- or high-intensity categorization of the individual (Supplementary Table S2).

The patients undertook daily aerobic training sessions using a pedal exerciser, as well as strength training using ankle weights and dumbbells adjustable from 0.5 kg to 2.5 kg, twice a week on non-consecutive days for 30 min per session.

The loads were modulated by monitoring heart rate and the Borg scale, ensuring patients were receiving pharmacological therapy and verifying the absence of adverse symptoms. The treatment program was delivered via tele-rehabilitation using a dedicated platform.

For the high-level exercise group, the intensity was tailored to 70–80% of the theoretical maximum heart rate and with a Borg score of 3 to 5 on the CR10 scale, as this is more easily understood than the Borg RPE scale.

For the low-level exercise group, the targets were lower: 40–70% of the theoretical maximum heart rate, but with the same weekly frequency, starting with 10 min per session and increasing to 30 min if tolerated.

The intensity of the exercises was reassessed at every session, i.e., twice a week.

REMOTE PHYSIOTHERAPY TREATMENT PROTOCOL

Connect online with the patient via the platform;Instruct the patient to wear the monitoring devices the patient has previously been trained to use;Take the basal parameters with the patient sitting at rest for at least 5 min: detect heart rate, peripheral saturation, basal pressure and subjective sensation of effort using the Borg CR10 scale and enter them into a specific database;Remote training with exercises based on FITT principles: frequency, intensity, time, type and progression of the exercise according to the patient’s functional level;Take vital signs at the end of the session with the patient seated.

LOW LEVEL

Patients started training sessions with 30 min of callisthenic exercises, followed by a free effort reconditioning with the use of a seated pedal set without load for 10/15/20/30 min based on the patient’s clinical condition. In addition, a suggested free walk session of at least 10 and at most 30 min per day was set and monitored via a pedometer.

HIGH LEVEL

The sessions included 30 min of fatigue-tolerant resistance exercises with dumbbells and ankle cuffs with 2 sets of 15 repetitions. In addition, approximately 30 min of free endurance training on a cycle ergometer (EverFit Welly M), trying to achieve a Borg CR10 between 3/10 and 5/10, with 5 min of warm-up, 20 min of activity and 5 min of cool-down, was performed. The adequate workload was achieved gradually according to the FITT method (Supplementary Table S2).

### 2.20. Sample Size Estimation

From the literature, frailty at discharge is expected to be about 40% in the overall study population [17,18]. We expect frailty reversal in Groups A and B of 48% and 15%, respectively [8], so frailty at the end of follow-up is hypothesized to be 21% in Group A and 34% in Group B. To achieve 80% power in detecting a 13% difference in frailty prevalence between Groups A and B after the intervention, with an alpha error of 5%, a sample size of 370 subjects is needed. Considering about a 22% dropout rate, a total of 450 patients are required.

Considering that recent trials do not consider frailty as a binary outcome, but as a continuous variable [23], and that an improvement of 1 unit in the EFT scale is associated with a 28% lower mortality incidence and thus represents a clinically meaningful phenomenon [11], we also calculated the sample size needed to observe a difference in the mean level of EFT between the two groups. Considering that: 1—using real data collected in our units in other similar studies, the mean EFT at baseline is 2.25 ± 1.25; 2—assuming an improvement of 1 unit (minimal clinically important difference, i.e., the smallest difference in score that benefits the patient) and therefore a mean score at the end of the study of 1.25 ± 1.25 [11]; 3—assuming a power of 90% and alpha of 5%; and 4—assuming a 30% improvement in the control group treated with the standard of care (and thus expecting a mean EFT of 1.95 in this group) and maintaining the same SD for all, it follows that 136 individuals are needed to observe a difference in the mean level of EFT score at the end of the trial. Considering also a 22% possible dropout rate, a sample size of 166 people is needed for this analysis. The same calculation using the SPPB as the metric of interest provided similar results.

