## 4. Discussion

The efficacy of eHealth-based, home-delivered CR interventions on frailty is debated [7]. To address this gap, we designed a randomized trial evaluating whether an eHealth CR program, compared with standard care, can reduce the prevalence or degree of frailty in patients >65 years hospitalized for AHF or ACS. Here we outline the trial protocol and report the baseline characteristics of the enrolled participants.

The number of enrolled individuals is lower than the planned sample size for the primary outcome, but sufficient for the co-primary outcomes. Thus, the study will be powered to detect a difference in the mean level of frailty but not to observe a difference in the prevalence of frailty considered as a binary variable, unless a higher-than-expected efficacy of the intervention emerges. Indeed, the study now reaches a power of 55% for the primary outcome when considering an expected difference of 13% in the final prevalence of frailty, while a difference of 17% in the prevalence of frailty would be needed to obtain a significant result. This aspect is of relevance, especially in case of non-significant findings.

The lower-than-expected enrollment capacity is attributable to the high rate of refusal to participate due to the reported inability or fear of using technological devices such as a tablet. These phenomena commonly, referred to as “digital illiteracy” and “technophobia”, are common in the oldest old and particularly pervasive in Italy [24]. As a result, we had to amend the protocol after the start of the study to lower the cutoff for age of inclusion in the study. We believe that this does not represent an issue since, as discussed, frailty represents a continuum with a broad spectrum of conditions that should be addressed as early as possible and not only when severe comorbidities are present [9,10]. In this respect, this consideration also emphasizes the relevance of the results, which will demonstrate whether an eHealth-based, multidomain intervention is able to affect the degree of frailty when considered as a continuous, and not binary, variable.

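### Both dropout allowances multiply by 1.22 instead of dividing by 0.78: at the stated 22% dropout, 450 and 166 should be 475 and 175

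*Protocol article*

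**What the plan says.** Section 2.20 (Sample Size Estimation) contains two calculations.

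- **Frailty prevalence:** "frailty at the end of follow-up is hypothesized to be 21% in Group A and 34% in Group B". At 80% power and 5% alpha, "a sample size of 370 subjects is needed". The allowance for loss follows: "Considering about a 22% dropout rate, a total of 450 patients are required".
- **Mean EFT:** the intervention arm is assumed to reach "a mean score at the end of the study of 1.25 ± 1.25" and the control arm 1.95 with the same SD. At 90% power and 5% alpha this gives 136 individuals, and then: "Considering also a 22% possible dropout rate, a sample size of 166 people is needed for this analysis".

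For SPPB, the section says only that the same calculation came out similarly. It prints no difference, SD or number. Section 2.22 restricts the SPPB analysis to patients measured at both time points, and Table 2 shows a baseline SPPB for 171 of 206 patients. The Discussion says that enrolment fell short of the target for the primary outcome "but sufficient for the co-primary outcomes".

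**The concern.** A dropout rate is a share of those enrolled. To be left with a required number after losing 22%, one divides that number by 0.78. Adding 22% to it gives too few patients. Both printed totals look like the second operation, so neither would deliver its stated power at its stated dropout.

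This matters because 166 is the only enrolment benchmark printed for the co-primary means. Section 2.2.1 relies on the power for those means when it makes frailty prevalence exploratory, and the Discussion repeats that enrolment suffices for them. A reader who checks that statement will use 166.

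**Working it through.** **Inputs (Section 2.20):** 21% v 34%, 80% power; difference 1.95 − 1.25 = 0.70, SD 1.25, 90% power; alpha 5%; dropout 22%. Allocation is 1:1 (Section 2.21). The article does not say whether alpha is one- or two-sided; two-sided reproduces its figures.

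**1. Base sizes.**

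- Proportions, pooled normal formula without continuity correction, mean proportion 0.275: n per arm = [1.960·√(2·0.275·0.725) + 0.842·√(0.21·0.79 + 0.34·0.66)]² / 0.13², just over 184, so 185 per arm and 370 in total. This agrees with the article.
- Means: n per arm = 2·(1.960 + 1.282)²·1.25² / 0.70², just over 67, so 68 per arm and 136 in total. This agrees with the article, and a t-test calculation also gives 136.

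**2. Dropout step.**

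| Evaluable | × 1.22 | Printed | ÷ 0.78 | Correct total |
|---|---|---|---|---|
| 370 | 451.4 | 450 | 474.4 | 475 |
| 136 | 165.9 | 166 | 174.4 | 175 |

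Multiplication reproduces both printed totals; division reproduces neither. Equal arms would make the totals 476 and 176.

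**3. What the printed totals deliver at 22% dropout.**

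- 450 × 0.78 = 351 evaluable, 19 short of 370. Power is 78.1%.
- 166 × 0.78 = 129.5, so 129 evaluable, 7 short of 136. Power is 88.4% (t-test) to 89.0% (normal approximation).

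**4. Dropout that the printed totals do cover.** 1 − 370/450 = 17.8% and 1 − 136/166 = 18.1%.

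**5. EFT at actual enrolment.** Both 209 randomized and the 206 in Table 2 exceed 175. From 206, 206 × 0.78 = 160.7, so 160 evaluable, with power of about 94%.

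**6. SPPB, under two assumptions.** Suppose that SPPB also needs 136 evaluable at the same standardised effect (0.70/1.25 = 0.56), and that a further 22% of the 171 patients with a baseline value are lost. Then 171 × 0.78 = 133.4, so 133 remain, 3 short of 136. Power is 89.4% (t-test) to 89.9% (normal approximation). The shortfall disappears if SPPB needs 133 evaluable or fewer, or if loss among the 171 is at most 1 − 136/171 = 20.5%.

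**The case against.** The strongest reply is that nothing downstream changes. The 22% is a planning guess, worded as approximate in one place and as possible in the other, and the totals are right for about 18%. Enrolment has closed. The prevalence target was missed by far more than 25 patients, and the Discussion already discloses power of 55% for it. The EFT target is met on either figure. All of this stands and limits the weight of the point. It does not make the printed figures consistent: the EFT total matches 136 × 1.22 to the unit, so rounding or approximate wording does not explain it.

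A reader might go further. Since 171 patients have a baseline SPPB, which is above 166 but below 175, the reader might infer that correcting the arithmetic turns sufficiency for SPPB into insufficiency. The documents do not support that, for three reasons.

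- The 175 comes entirely from EFT inputs. A similar SPPB result need not be an equal one, and the gap is only 4 patients.
- Taking 22% from the 171 adds a second loss to the 35 of 206 already without a baseline value. The article does not say whether its 22% includes missing assessments.
- The calculation is unadjusted, while the planned analyses adjust for sex and baseline SPPB. On the usual 1 − r² reduction in variance, 1 − r² = 133.4/136 gives r of about 0.14, so even a weak correlation between baseline and follow-up would make up the difference.

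**Conclusion.** The error is certain and occurs twice: at 22% dropout the totals are 475 and 175, not 450 and 166. The shortfalls are 25 and 9 enrolled patients, costing about 2 points of power for prevalence and 1 to 2 points for mean EFT. This rests only on the printed dropout rate and on base sizes that reproduce.

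The statement that enrolment suffices holds for EFT. For SPPB it is neither shown nor refuted. Total enrolment is the wrong yardstick there, because the analysis set cannot exceed 171 and the SPPB requirement is not printed. Under the two assumptions in the check, power would be about 89–90% against 90%, which is marginal.

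**What to change.** In Section 2.20, either restate the totals as 475 and 175 (476 and 176 for equal arms), or keep 450 and 166 and say that they allow for about 18% dropout. State there the SPPB difference, SD and evaluable number that were used.

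In the Discussion, separate the two co-primary means. Say that 209 enrolled exceeds 175 for EFT, and give the SPPB power from its own inputs with 171 as the upper limit on evaluable patients. The text should not say that 171 falls short for SPPB unless the SPPB calculation shows it.

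The cost is two numbers, one line of SPPB inputs that the sponsor must already hold, and one reworded sentence. No further enrolment and no change to the analysis are needed.

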### 2.2. Study Endpoints

#### 2.2.1. Primary Endpoints

The primary endpoint is to assess whether a home-based TR program significantly reduces the prevalence of frailty in comparison to usual care in older individuals hospitalized for ACS and/or AHF. Frailty status is defined as having an Essential Frailty Toolset (EFT) score (ranging from 0 to 5) ≥ 3 [8].

Since the recent literature suggests that frailty is a progressive continuum and not a present/absent condition [9,10] and considering that small improvements in the degree of frailty are associated with tangible benefits [11], the mean degree of frailty was considered as a co-primary endpoint. In particular, mean differences between groups at the end of treatment in the EFT and Short Physical Performance Battery (SPPB) scales were set as co-primary outcomes after the start of the enrollment due to the considerations reported above. After termination of the enrollment, we observed that the study is powered to detect a difference in these co-primary outcomes, while the power for the primary outcome of frailty prevalence is lower than initially planned. Thus, this and the other secondary endpoints will be considered as exploratory.

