### 2.22. Data Collection and Statistical Analysis

Study data were collected in the eCRF of an electronic web-based database, where each patient is identified by a randomly assigned alphanumeric code that is center-specific.

Baseline data were analyzed through descriptive analyses. Results for the overall population and for both Groups A and B are presented. Categorical variables were presented as frequencies and percentages and compared between the two groups by Chi-square test of Fisher’s exact test. Continuous variables were summarized by mean ± standard deviation and tested for normality distribution by Kolmogorov–Smirnov test. Since all variables were not normally distributed, the non-parametric Wilcoxon–Mann–Whitney U test will be used to compare baseline variables between groups. The prevalence of frail patients in the two groups is indicated as an EFT score ≥ 3. For the planned analyses, mixed models, adjusted for unbalanced variables, will be used to account for different times to follow-up. Only people with available measures of EFT at both baseline and follow-up will be included in the analyses relative to the prevalence of frailty and EFT as a continuous variable, while only individuals with available measures of SPPB at both baseline and follow-up will be included in the analyses for this endpoint. For the other covariates, missing data will be imputed through regression models. Given the limited sample size, subgroup analyses are not planned.

All analyses were performed by using SAS Software version 9.4. Tests will be considered significant for a *p* value < 0.05.

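### The claim that the trial is powered for the SPPB co-primary has no stated basis; on the trial's own SD and counts, 90% power needs about 1.75 to 2.0 points unadjusted

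*Protocol article*

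**What the plan says.** Section 2.20 sets out the EFT calculation in full: "the mean EFT at baseline is 2.25 ± 1.25", "therefore a mean score at the end of the study of 1.25 ± 1.25" with the intervention, and for usual care "thus expecting a mean EFT of 1.95 in this group", with the same SD throughout and "assuming a power of 90% and alpha of 5" per cent. This gives 136 evaluable patients, or 166 after the allowance for dropout. The SPPB receives one sentence: "The same calculation using the SPPB as the metric of interest provided similar results".

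Section 2.2.1 makes the mean EFT and mean SPPB co-primary after enrolment had begun. It then reports that, once enrolment had ended, "we observed that the study is powered to detect a difference in these co-primary outcomes", and it demotes frailty prevalence to exploratory because its power is lower. The Discussion repeats that enrolment is sufficient for the co-primaries.

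On the data available, section 2.19 says "All included individuals were subjected to the Short Physical Performance Battery (SPPB) to also evaluate balance and fall risk", and step 1 of section 2.5 likewise has patients assessed on both scales before discharge. Table 2 nevertheless shows SPPB for 171 of 206, with mean 8.71 and SD 3.51. Section 2.22 then provides that "only individuals with available measures of SPPB at both baseline and follow-up will be included in the analyses for this endpoint", while missing values of other covariates are imputed by regression.

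**The concern.** The power statement carries weight. It is the stated reason for resting the confirmatory analysis on the two mean scores rather than on prevalence. For EFT a reader can check it. For SPPB there is nothing to check: no target difference, SD or number. The statement was also made after enrolment closed, when the SPPB spread and the number of baseline values could be known, and both appear in the same article without being connected to it.

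If the planned SPPB effect was well below 2 points, a null SPPB result would be read as adequately powered evidence of no effect when it is not. Separately, the rule requiring both values removes 35 patients from a co-primary analysis before any dropout, because of a missing covariate rather than a missing outcome.

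**Working it through.** **1. Reproduce the EFT figure.** Inputs from section 2.20: difference 1.95 − 1.25 = 0.70, SD 1.25, alpha 5%, power 90%. The article does not say whether the test is one- or two-sided; two-sided is used here because it reproduces the stated number.

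n per arm = 2 × (1.960 + 1.282)² × 1.25² / 0.70² = 67.01, rounded up to 68, so 136 in total. This matches the article (the t-based solution is 135.97). The 166 is 136 × 1.22.

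With 206 × 0.78 ≈ 161 evaluable, power for that EFT effect is about 94%, so on its own inputs the EFT half of the claim holds.

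**2. What similar results means for SPPB.** About the same number implies about the same standardised difference: 0.70 / 1.25 = 0.56. At the observed SD this is 0.56 × 3.51 = 1.97 points. By contrast, a 1-point target with 136 patients and 90% power would need an SD of about 1.8, roughly half the observed value.

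**3. Detectable difference for the SPPB analysis set.** At most 171 patients can enter; with the article's 22% dropout, 171 × 0.78 ≈ 133. For total N in two equal arms, difference = (z for alpha + z for power) × SD × √(4/N). With SD 3.51 and two-sided 5%:

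| Evaluable N | 90% power | 90%, t-based | 80% power |
|---|---|---|---|
| 171 (no dropout) | 1.74 | 1.75 | 1.50 |
| 133 (22% dropout) | 1.97 | 1.99 | 1.71 |

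The arm-specific SDs in Table 1 (3.46 and 3.55) change the 133-patient figure only to 1.95 and 2.00.

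**4. Power for smaller effects.** The article gives no SPPB target, so these effects are illustrative assumptions.

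| True difference | N = 133 | N = 171 |
|---|---|---|
| 1.0 point | 38% | 46% |
| 1.5 points | 69% | 80% |
| 2.0 points | 91% | 96% |

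**5. Allowing for the planned baseline adjustment.** The Discussion says the analyses will be adjusted for sex and SPPB. With correlation r between baseline and follow-up SPPB, the SD is multiplied by √(1 − r²). The article gives no r; 0.5 to 0.8 is assumed.

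| Assumed r | Adjusted SD | 90% power, N = 133 | 90% power, N = 171 |
|---|---|---|---|
| 0.5 | 3.04 | 1.71 | 1.51 |
| 0.6 | 2.81 | 1.58 | 1.39 |
| 0.7 | 2.51 | 1.41 | 1.24 |
| 0.8 | 2.11 | 1.18 | 1.04 |

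**6. Who lacks a baseline value.** If a is the number in the intervention arm with SPPB, then 9.11a + 8.27(171 − a) = 8.71 × 171, so a = 171 × 0.44 / 0.84 ≈ 90, leaving about 81 controls. Out of 103 per arm, about 13 intervention and 22 control patients lack the value. These counts come from rounded means and could each move by a patient or two, but the imbalance remains.

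**The case against.** The strongest reply is that no wrong figure has been shown. If the planners assumed about 2 points on the SPPB, the sentence in section 2.20 is right, and 133 evaluable patients give about 90% power for it. The article is a condensed account, and the deposited protocol may contain the SPPB inputs. This stands as far as it goes. A reader might infer that the trial is underpowered for SPPB, and the documents do not support that: they give no minimal important difference for SPPB, and a standardised effect of 0.56 is the one already assumed for EFT. What the reply does not meet is that the article itself asserts adequate power after enrolment, and nothing in it connects that assertion to its own SD and count.

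Second, the 2-point figure is for an unadjusted comparison, whereas adjustment for baseline SPPB is already planned. This also stands. The unadjusted figure is a fair check of section 2.20, whose method is unadjusted, but the planned analysis will do better by an amount that depends on an unstated correlation.

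Third, a reader might set 133 against the 136 in section 2.20 and see a shortfall. It is negligible: at a standardised difference of 0.56, power is 89.4% with 133 and 90.0% with 136. By the article's own inflation the requirement is 166, which 171 exceeds.

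Finally, a reader might conclude that SPPB should be tested only after EFT. That is a question of multiplicity and does not follow from a gap in the power statement.

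**Conclusion.** The power claim for the SPPB co-primary is unsupported as written; it is not shown to be false. On the observed SD and the method of section 2.20, it holds for a difference of about 1.75 points (all 171 followed up) to 2.0 points (133 evaluable). With the planned baseline adjustment, the figure at 133 falls to about 1.7 to 1.2 points for an assumed correlation of 0.5 to 0.8.

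This rests on three assumptions: the follow-up SD equals the baseline SD, as section 2.20 assumes for EFT; the 22% dropout applies to the 171 patients with baseline SPPB; and the test is two-sided at 5%.

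Separately, 171 of 206 does not agree with the statement that everyone was tested. The both-values rule then discards patients for want of a covariate, apparently unevenly between the arms.

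**What to change.** - In section 2.20, replace the SPPB sentence with the assumed difference, SD and, if adjustment is relied on, the baseline-to-follow-up correlation.
- Restate power, or the detectable difference, for the number of patients expected in the SPPB analysis, and qualify the claims in section 2.2.1 and the Discussion to match.
- Reconcile section 2.19 with the 171 in Table 2, and report missing baseline SPPB by arm.
- In section 2.22, keep patients who have follow-up SPPB but no baseline SPPB, imputing the baseline from other baseline data as is already planned for other covariates. The gain depends on how many of the 35 have a follow-up SPPB, which is not stated. If 78% did, about 161 would be evaluable and the unadjusted 90% figure would fall from 1.97 to 1.79 points.

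The cost is a few sentences and one change to the analysis-set rule, best made before outcomes are compared by arm. The stated power for SPPB may look less favourable.
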